## 9.2 Randomization, blinding and treatment allocation

Not applicable

## 9.3 Study procedures

The targeted screening will be performed in the pharmacies and general practices that included the subjects. The visit and cardiovascular risk factor measurements will be performed by GPRI or the University Medical Center Groningen. Albuminuria measurements will be performed by the University Medical Center Groningen.

### Targeted screening phase

Pharmacies and GPs select potential subjects based on the medical history and last 6 months of prescriptions and registered indications, as described in section 5.2. During this phase subjects will be asked to give written informed consent to participate in the study. Subjects will collect urine samples using the PeeSpot and sent the samples to the laboratory. Furthermore, they receive a questionnaire to collect subject characteristics. The informed consent form and the subject characteristics questionnaire are sent to the General Practitioners Research Institute (GPRI). GPRI will receive the results of the urine tests. If albuminuria is elevated, subjects receive a second PeeSpot to perform a confirmational measurement. If subjects are recruited via GPs and have an elevated albuminuria measurement performed less than 11 months ago, only one extra albuminuria measurement is necessary.

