**Novel aspects**

1. It is currently unknown how many subjects are undiagnosed with elevated albuminuria and are thus at a high risk of chronic kidney disease progression.
2. It is unknown which approach to case finding is more (cost) effective in identifying undiagnosed albuminuria in primary care. This study will guide future larger scale programs.
3. It is unknown how many subjects have persistent albuminuria despite adequate treatment with renin-angiotensin system (RAS) inhibitors
4. 4. It is unknown whether the cardiovascular risk monitoring and treatment of subjects change after participation in primary care screening for albuminuria

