#### Potential overlap

Potential overlap in subject recruitment occurring when participating pharmacies are providing services to subjects of also participating general practitioners will be avoided as much as possible. In case of known overlap at the recruitment phase, data available from the general practitioner will be preferred. All subjects being registered as a patient from a participating GP in the pharmacy database will be excluded from the selection list from the pharmacy.

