## 9 METHODS

### 9.1 Study endpoints

#### 9.1.1 Primary endpoints

1. Elevated albuminuria, defined as a urinary albumin creatinine ratio (UACR)  $\geq 3.0$  mg/mmol.
2. Average screening costs per subject that was identified as having kidney disease by screening for albuminuria. All costs considered are mentioned below (Table 1)

Table 1. Costs associated with screening

|                                                                             |
|-----------------------------------------------------------------------------|
| Costs of the PeeSpot                                                        |
| Laboratory costs                                                            |
| Printing and postal mailing costs of all invitations and needed information |
| Labor costs needed to recruit and start GP's and pharmacies                 |
| Labor costs of training GP's and pharmacies                                 |
| Costs of extracting patients eligible for inclusion                         |

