## **11 STATISTICAL ANALYSIS**

Characteristics of subjects recruited will be described as mean values with standard deviation or median with interquartile range for continuous variables. Categorical variables will be described as numbers and percentages of the subjects per category.

The overall prevalence of elevated albuminuria, and prevalences of unrecognized and persistent elevated albuminuria despite a RAS-inhibitor are described as percentages with 95% confidence intervals. The number of eligible patients from general practices who fulfilled the inclusion criteria but had an albuminuria level  $<3$  mg/mmol recorded within 18 months prior to selection (and where therefore not invited to participate), will be included in the denominator to calculate the prevalences.

To compare effectiveness and costs of screening on elevated albuminuria in pharmacies and in GP-care, the costs for the targeted screening strategies in both pharmacies and GPs will be calculated.

For each approach, all costs associated with the screening will be added and divided by the total number of subjects identified with confirmed elevated albuminuria. A screening-

approach will be considered more effective than the other if the costs per identified patient are  $\geq 10\%$  lower.

Frequencies of cardiovascular monitoring and treatment changes are summarized as numbers and percentages with 95% confidence intervals.

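### The cost-per-case comparison counts patients whose elevated albuminuria was already on record, and Section 9.3 confirms such GP recruits on one measurement, while the protocol elsewhere frames the question as finding undiagnosed disease

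*Protocol*

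**What the plan says.** **Denominator and decision rule.** In Section 11, for each route, "all costs associated with the screening will be added and divided by the total number of subjects identified with confirmed elevated albuminuria". One "approach will be considered more effective than the other if the costs per identified patient are" at least 10% lower. Nothing takes out cases already on record.

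**Who is invited.** Sections 4.1 and 5.3 leave out only patients with a recent normal result. Known elevated albuminuria is no exclusion, and Table 2 in Section 11 counts GP patients with an elevated value in the last 11 months. Pharmacy lists come from dispensed medication and registered indications (4.1, 5.2.1), without an albuminuria result.

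**Confirmation.** Section 9.3 states that if subjects come in through a GP and "have an elevated albuminuria measurement performed less than 11 months ago, only one extra albuminuria measurement is necessary". Otherwise two elevated PeeSpots are needed, with a third kit if the second is normal (Summary, study methods). The Summary (burden and risks), Section 4.1 (PeeSpot screening) and Section 8.1.1 also waive the second measurement after a recent elevated value, but do not clearly limit the waiver to GP recruits.

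**Purpose.** Under Novel aspects the Summary says: "It is unknown which approach to case finding is more (cost) effective in identifying undiagnosed albuminuria in primary care". Section 2 lists the unrecognized proportion among the facts needed to judge cost-effectiveness. Primary objective 2 (3.1) speaks only of identified patients with elevated albuminuria, and 9.1.1 of subjects "identified as having kidney disease by screening for albuminuria". Unrecognized disease is defined in 9.1.2 as a secondary endpoint and is not carried into the cost comparison.

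**The concern.** A patient whose practice recorded an elevated value some months ago adds a full case to the denominator, although the practice gains no new diagnosis. If such patients are unevenly spread over the routes, or are easier to confirm in one of them, the cost per case no longer measures how cheaply each route finds undiagnosed disease.

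The result feeds a yes/no rule with a 10% margin. The Summary says the study will guide larger programmes, and Section 4 foresees a possible amendment to extend screening. A ranking that partly reflects known patients could be read as a ranking on undiagnosed ones.

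The protocol itself fixes both the denominator and the rule, so this is not detail merely left to a statistical analysis plan.

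**Working it through.** The protocol gives no cost per case, unit price, response rate or known share, so there is no figure to reproduce. Every share and rate below is an assumption, except the 10% margin (Section 11) and the confirmation rules (9.3, Summary).

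**A. Counting known cases.** Let f be the share of a route's confirmed cases already on record.

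- Cost per newly found case = cost per confirmed case / (1 − f).
- The GP/pharmacy cost ratio is therefore multiplied by (1 − fP)/(1 − fG).

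Start from 0.90, where the GP route just meets the rule:

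| fG | fP | Multiplier | 0.90 becomes |
|---|---|---|---|
| 10% | 0 | 1/0.90 = 1.111 | 1.00 |
| 19% | 0 | 1/0.81 = 1.235 | 1.11 |
| 20% | 10% | 0.90/0.80 = 1.125 | 1.01 |
| 30% | 10% | 0.90/0.70 = 1.286 | 1.16 |
| 20% | 20% | 1.000 | 0.90 |
| 10% | 20% | 0.80/0.90 = 0.889 | 0.80 |

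At 1.11 the pharmacy route is 10% cheaper (1/1.11 = 0.90) and the verdict reverses. Equal shares change nothing. A higher pharmacy share moves the ratio the other way.

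**B. The single-measurement rule alone.** Take two identical populations of 1,000 invited and apply the waiver in the GP arm only. Assume 40% response, 8% true prevalence, a 3% false-positive rate per test, a laboratory test costing half a kit, and no fixed costs. Let s be the chance that a true case tests positive and t the return rate of follow-up kits.

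Worked case, with 20% of true cases known, s = 0.85, t = 0.90:

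- True cases among responders: 1,000 × 0.40 × 0.08 = 32, of whom 6.4 are known and 25.6 new.
- Chance of confirmation after a first positive, by second or third kit: 0.9 × 0.85 + 0.9 × 0.15 × 0.9 × 0.85 = 0.868.
- New cases confirmed, either arm: 25.6 × 0.85 × 0.868 = 18.9, plus 0.6 false positives.
- Known cases confirmed: GP 6.4 × 0.85 = 5.44; pharmacy 5.44 × 0.868 = 4.72.
- Totals: GP 24.9, pharmacy 24.2. Total cost ratio: 0.993.
- Cost per confirmed case, GP/pharmacy: 0.993 × 24.18/24.89 = 0.964.

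Over s = 0.75 to 0.95 and t = 0.80 to 0.95:

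| Known share of true cases | GP advantage from the waiver |
|---|---|
| 10% | 1–4% |
| 20% | 2–8% |
| 30% | 3–11% |
| 50% | 5–17% |

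The GP route gains in every scenario. The saved kits account for only 0.3–1.8% of total cost, because every invitee gets a first kit. Most of the gain arises because known cases are not lost at the second or third kit.

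**C. The two parts together.** In the worked case the waiver raises the known share among confirmed cases to 5.44/24.89 = 21.9% (GP) against 4.72/24.18 = 19.5% (pharmacy). The multiplier from A is 0.805/0.781 = 1.03, and 0.964 × 1.03 = 0.993. Counting only new cases brings the ratio to 0.98–1.00 in every scenario, as it should be for identical populations.

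**The case against.** The strongest reply is that Section 11 follows its objective. Primary objective 2 and the Summary endpoint concern identified elevated albuminuria, and the word undiagnosed appears only under Novel aspects. Known but undertreated patients are also of interest: secondary objective 2 concerns albuminuria persisting on RAS inhibitors. Each counted GP case still needs an elevated study PeeSpot, so it is in a sense found by screening, and the earlier practice test is usual care. This stands far enough that the planned denominator cannot be called wrong for the objective as worded. It does not remove the mismatch with Novel aspects and Section 2.

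Stronger readings that a reader might infer are not supported:

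- *Counting known cases always favours GPs.* Known cases stay in both denominators. Pharmacy recruits all receive medication, whereas GP lists add obesity and coded, possibly untreated, disease. Pharmacy recruits could be the more closely monitored group, so the sign is unknown.
- *Pharmacy recruits can never use the waiver.* Only 9.3 ties it to GP recruits. The other three places do not, so they need reconciling.
- *The waiver by itself decides the comparison.* Within the ranges tried, it passes 10% only at a known share of 30% or more with poor repeat positivity and kit return, or at about 50% with the poor values still needed: the central case there gives 0.915.
- *The overlap rule adds a further bias.* It says "All subjects being registered as a patient from a participating GP in the pharmacy database will be excluded from the selection list", which could spread pharmacy start-up costs over fewer cases. But it prevents double counting, and the protocol gives neither the overlap nor the fixed-cost share, so no size can be attached.

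**Conclusion.** The concern holds in limited form. The protocol's statements of what the cost comparison is meant to show do not agree, and its primary ratio cannot separate finding new cases from re-finding recorded ones. The confirmation rule as written in 9.3 favours the GP route. The direction of the effect of counting known cases depends on shares that the protocol does not give.

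On assumed shares, a ratio of 0.90 becomes anything from 0.80 (fG = 10%, fP = 20%) to 1.16 (fG = 30%, fP = 10%). The 10% margin can be crossed in this way, but not necessarily. It would be wrong to conclude that the planned comparison is known to be biased toward GPs by any stated amount. Inflating the GP figure alone by 1/(1 − fG) is likewise not a comparison, because the pharmacy figure must be corrected too.

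**What to change.** 1. In 9.1.1 and 11, report cost per unrecognized confirmed case for each route beside cost per any confirmed case, using the 9.1.2 definition. First reconcile that definition with the Summary, where self-report and record are joined by *or* instead of *and*.
2. State that a route will not be called more effective at finding undiagnosed albuminuria unless the 10% rule also holds on the unrecognized-case figure. Align Novel aspects, Section 2 and primary objective 2 accordingly.
3. Judge prior recognition alike in both routes by checking the GP record of each pharmacy-route positive. The Appendix A questionnaire already asks for the subject's GP and for known protein in the urine, and Section 4.3 already plans data extraction from GPs and/or pharmacies.
4. Reconcile 9.3 with the Summary, 4.1 and 8.1.1 so that one confirmation rule applies to both routes in the cost comparison.

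**Cost:** wording changes and one record check per pharmacy-route positive. The added ratio rests on fewer cases and is less precise. For illustration, if 20% of the 112 patients targeted for the elaborated screening phase were already known, 112 × 0.80 ≈ 90 would remain across both routes. The planned figure is kept, so nothing is lost.

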### Elaborated screening phase

In case of elevated albuminuria, subjects will be invited to attend an elaborated screening visit with a researcher of GPRI at the pharmacy, GP practice or other convenient location near the subject.

The following data will be collected by interview:

1. Medical history of
  - a. Kidney disease
  - b. Albuminuria
  - c. Diabetes Mellitus, type 1 or 2, including a history of keto-acidosis

- d. Cardiovascular disease
  - e. Hypertension
  - f. Lipid disorders
2. Medication use over the last 6 weeks
3. Medication adherence measured with the medication adherence report scale-5 (MARS-5) (appendix 16.3)
4. Smoking status, never, current, or ex-smoker

The following data will be collected by measurement:

1. Pulse rate
2. Systolic and diastolic tension (mean of 3 measurements)
3. Height
4. Weight (kg)
5. Creatinine and HbA1c in capillary blood

A report will be sent to the general practitioner based on these findings. The general practitioner will be advised to follow the NHG guidelines for cardiovascular management (Appendix 0) and to adjust treatment, if necessary.

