**Study methods:** For this study subjects will be recruited for a targeted screening via pharmacies and general practitioners. For the pharmacies, subjects at risk of albuminuria will be identified as those with a prescription for Diabetes Mellitus, hypertension or lipid disorders. For general practitioners, subjects who have Diabetes Mellitus, cardiovascular disease, hypertension, lipid disorders, or obesity will be selected from electronic medical records. For the targeted screening, subjects are asked to collect urine at home for an albuminuria measurement. In case of elevated albuminuria, subjects will receive a second collection device for a confirmational measurement. If elevated albuminuria is confirmed, subjects will be invited for an elaborated screening visit. Elevated albuminuria will be defined as an urinary albumin creatinine ratio (UACR)  $\geq 3.0$  mg/mmol on two occasions in accordance with the prevailing primary care guideline ("NHG Standaard Chronische Nierschade"). If not confirmed, they will receive a third collection device. If the third collection device shows normal albuminuria, the study ends. In case of elevated albuminuria, subjects will be invited for an elaborated screening visit. During this screening visit, cardiovascular risk factors will be assessed, and medication use will be reviewed. A review report following the Dutch primary care guidelines will be provided to the subjects' general practitioner (GP). We aim to examine at least 112 patients with elevated albuminuria at the elaborated screening phase in this study. In the pilot, 57 patients with elevated albuminuria were screened in the elaborate screening phase. These patients were included from 2 pharmacies and 3 general practitioners. For the proposed extension, the pharmacies will be scaled up to a total of 5 and general practitioners to a total of 10. Six months after the study

visit, the frequency of cardiovascular monitoring and treatment changes via medication prescriptions will be monitored via data extraction of the general practitioners and/or pharmacies.

We assume that at least 6300 patients from general practices and pharmacies will be eligible for inclusion in the screening phase.

The costs of both screening approaches per identified patient with elevated albuminuria will be evaluated and compared.

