#### Secondary endpoints

1. Unrecognized chronic kidney disease, defined as elevated albuminuria, not reported by the subject or previously recorded in electronic medical records of the subjects' general practice or pharmacy.
2. Persistent elevated albuminuria, defined as elevated albuminuria persisting despite good adherence (score  $\geq 4$  (doses seldom or never missed) reported in MARS) to treatment with RAS-inhibitors for at least 6 weeks prior to elevated albuminuria assessment.
3. Changes in frequency of cardiovascular risk factor monitoring, defined as the difference between the frequency of cardiovascular risk factor monitoring in participants 3 years before and 6 months after targeted albuminuria screening.
4. Changes in cardiometabolic drug prescriptions, defined as changes in any prescription for cardiovascular disease or CKD 6 months after targeted albuminuria screening compared to 3 years before.

**Nature and extent of the burden and risks associated with participation, benefit and group relatedness:** All selected subjects will be asked to participate on a free-will base and to send a signed informed consent form with a completed short questionnaire to GPRI. They will be

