#### Albuminuria screening using PeeSpot

Selected subjects will receive an invitation to participate in the screening survey from their pharmacy or general practice by postal mail, including an informational letter about the study, an informed consent form, a short questionnaire to be completed (Appendix 16.1)

and a urine collection device (PeeSpot) with instructions. The participant will be asked to send the signed informed consent form and completed questionnaire and the collected urine to the General Practitioners Research Institute (GPRI) by postal mail (without costs). If the laboratory measures 'normal' albuminuria ( $<3.0$  mg/mmol), GPRI will inform the subject. In case of elevated albuminuria ( $\geq 3.0$  mg/mmol), GPRI will be informed to send a second PeeSpot for a confirmational measurement if informed consent has been received. If this second measurement is also elevated ( $\geq 3.0$  mg/mmol), subjects will be invited for an elaborated screening visit performed by GPRI (phase 2). A second confirmational measurement of elevated albuminuria will not be required when a recent (within 11 months) measurement performed by the general practice also indicated elevated albuminuria.

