#### **4.2 Phase 2: Elaborated screening phase**

When there is no elevated albuminuria at phase 1, a letter with the results will be sent to the participant, and no further actions from the participant are required. Subjects will be carefully informed about the results.

When elevated albuminuria is confirmed ( $\geq 3.0$  mg/mmol on two occasions), subjects are invited for an elaborated screening visit with a researcher. At the start of the visit, participants will be asked to provide informed consent. Next, CKD/CVD risk factors will be assessed and the participant's medication use, and medication adherence will be reviewed during an interview. GPRI will produce a report of their findings which will be shared with the general practice, including recommendations for additional measurements or treatment changes if applicable.

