#### 9.1.2 Secondary endpoints

1. Unrecognized chronic kidney disease, defined as elevated albuminuria, not reported by the subject and not previously recorded in electronic medical records of the subjects' general practice or pharmacy.
2. Persistent elevated albuminuria, defined as elevated albuminuria persisting despite good adherence to treatment with RAS-inhibitors for at least 6 weeks prior to elevated albuminuria assessment (score  $\geq 4$  on the Medical Adherence Report Scale (MARS)) (Appendix C, paragraph 16.3).
3. Change in frequency of cardiovascular risk factor monitoring, defined as the difference between the frequency of cardiovascular risk factor monitoring in participants 3 years before and 6 months after targeted albuminuria screening.
4. Changes in cardiometabolic drug prescriptions, defined as changes in any prescription for cardiovascular disease or CKD 6 months after targeted albuminuria screening compared to three years before.

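### The medication and adherence interview is anchored to the elaborated visit, not to the urine sample, so it does not cover the 6 weeks of RAS-inhibitor use that secondary endpoint 2 requires, and no other source is named

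*Protocol*

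**What the plan says.** The endpoint is defined twice. Protocol 9.1.2 requires good adherence to a RAS inhibitor "for at least 6 weeks prior to elevated albuminuria assessment". The Summary says the same: "treatment with RAS-inhibitors for at least 6 weeks prior to elevated albuminuria assessment".

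The data come later in the sequence. Under 4.2, once elevated albuminuria is confirmed, "subjects are invited for an elaborated screening visit with a researcher", and "medication adherence will be reviewed during an interview". Section 9.3 (Elaborated screening phase) lists the interview items. The one on drug use is "Medication use over the last 6 weeks", next to the MARS-5.

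Several steps can lie between the first elevated sample and that visit. Section 4.1 says that "GPRI will be informed to send a second PeeSpot for a confirmational measurement if informed consent has been received". The Summary adds a possible third round: "If not confirmed, they will receive a third collection device". For patients with an earlier practice result there is a shortcut: "A second confirmational measurement of elevated albuminuria will not be required when a recent (within 11 months) measurement performed by the general practice" was also elevated.

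No maximum interval from sample to visit is stated. Nor does the protocol say which of the two or three measurements is the assessment from which the 6 weeks are counted back.

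**The concern.** The two 6-week windows have the same length but end on different dates. The endpoint window ends at a urine sample; the interview window ends at the visit. Because the visit always comes after the sample, the interview misses the earliest part of the required window and records weeks after the sample that the endpoint does not ask about.

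At stake is one of the four secondary objectives, the prevalence of elevated albuminuria under adequate RAS inhibition, which the Summary also lists among the study's novel aspects. Recent starters can be counted as treatment not controlling albuminuria when they had not been treated long enough before the test. Adherent users who stopped between test and visit can drop out of the count. If dates are not collected at the visit, no later analysis of the interview data can restore them.

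**Working it through.** There is no plan figure to reproduce. The check compares two time windows.

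**Inputs**
- Required exposure: at least 6 weeks before the albuminuria assessment (Summary; 9.1.2).
- Recorded exposure: the last 6 weeks, asked at the visit (9.3).
- Gap g, in weeks from the reference sample to the visit: not given. Assumed range 1 to 12 weeks.

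**Formulas**, counting weeks back from the visit
- The required window runs from g + 6 to g; the recorded window runs from 6 to 0.
- Required weeks covered = max(0, 6 − g).
- Recall needed to cover the required window in full = 6 + g.
- A patient who started s weeks before the visit shows a full 6 weeks at interview if s ≥ 6, but had only s − g weeks of treatment before the sample. This patient is wrongly counted when 6 ≤ s < 6 + g.

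| g (assumed) | Required weeks covered | Recall needed | Start times wrongly counted (weeks before visit) |
|---|---|---|---|
| 1 | 5 of 6 | 7 | 6 to under 7 |
| 2 | 4 of 6 | 8 | 6 to under 8 |
| 4 | 2 of 6 | 10 | 6 to under 10 |
| 6 | 0 of 6 | 12 | 6 to under 12 |
| 12 | 0 of 6 | 18 | 6 to under 18 |

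Example with g = 4: a patient who started 7 weeks before the visit reports 6 full weeks of use but had 7 − 4 = 3 weeks before the sample.

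**The opposite error.** A patient treated throughout the 6 weeks before the sample who stopped between sample and visit meets the endpoint, but shows incomplete use in the interview window and can be excluded.

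**Who is unaffected.** A patient on the same RAS inhibitor from before week 6 + g up to the visit is classified correctly at any g, even with zero overlap. The table measures coverage of the window, not the rate of misclassification.

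**Adherence.** MARS is administered at the visit, and Appendix C gives no recall period, so the adherence half of the definition has the same anchoring problem.

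**Other sources in the protocol**
- The questionnaire sent with the first PeeSpot (Appendix A) has no medication item.
- Selection uses 6 months of dispensing data (5.2.1, 9.3), but 13.3 says GPRI cannot see the data of the eligible subjects to be invited.
- Endpoint 4 compares prescriptions with the three years before screening, which implies a history. The extraction in 9.3 (Implementation of care), however, describes data after the visit, and 4.3 describes the 6 months after screening.
- None of these is assigned to endpoint 2.

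**The case against.** The strongest reply is that the data may exist anyway. The three-year comparison in endpoint 4 requires a prescription history, and that history could date RAS-inhibitor treatment relative to any sample. This stands in part. It rules out saying that the endpoint cannot be derived correctly, which a reader might infer from the mismatch. It does not remove the gap: no section links those records to endpoint 2, the described extraction does not clearly reach back before the sample, and a prescription is not the same as adherent use.

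Second, most RAS-inhibitor users may be long-term users, for whom the windows give the same answer. That is fair. Only patients who start, stop or change around the test are affected, and the protocol gives neither that rate nor g.

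Third, one might infer that patients who start treatment after the first elevated PeeSpot are generally counted as persistent. At g = 2 or 4 weeks they are not: they have at most g weeks of use at the visit, so a 6-week item excludes them correctly. That error arises only once g exceeds 6 weeks. At shorter gaps the patients wrongly included started shortly before the sample.

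Fourth, one might read the 11-month practice value as an error in itself, because it may predate treatment. The text does not support this. A current elevated PeeSpot is still required, and a patient who was elevated months ago, was then treated, and is still elevated now fits the ordinary meaning of persistence. Calling it wrong assumes that the earliest value is the reference, which the protocol does not say. What remains is that the protocol does not name the reference.

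**Conclusion.** The concern holds in limited form. Endpoint 2 and the interview use windows that end on different dates. As written, the interview covers max(0, 6 − g) of the 6 required weeks, no other source is named, and the reference sample is not defined. Patients who started 6 to 6 + g weeks before the visit are wrongly included, and some who stopped between sample and visit can be missed.

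This rests on reading the interview item as counting back from the visit, which is its natural meaning in a list of data collected there, and on g being above zero, which the order of procedures guarantees. The values of g are assumptions. If the reference is the latest elevated sample, g is shorter and coverage better; if it is an old practice value, the interview may cover none of the required window.

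The effect on the reported prevalence cannot be estimated. For scale only: with the planned minimum of 112 visited patients, each misclassified patient is 1/112 = 0.9 percentage points of that group, and less in the wider denominator of Section 11. This is a descriptive secondary endpoint, and the primary endpoints are untouched. The change is still worth making before further visits, because dates not asked for at the visit cannot be recovered from the interview data.

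**What to change.** - **9.1.2 and Summary:** state which urine sample is the reference assessment for endpoint 2. Cover the case of two elevated PeeSpots, the case decided by a third, and the case where a practice value up to 11 months old replaces the confirmatory PeeSpot.
- **9.3, Elaborated screening phase:** replace the visit-anchored recall with RAS-inhibitor start and stop dates, and ask about adherence relative to the reference sample date. If a recall period is kept, it must reach 6 + g weeks back for each patient.
- **9.3, Implementation of care:** name GP and/or pharmacy prescription records from before the sample as the supporting source for endpoint 2, and state that extraction period, since the current text describes post-visit data.

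A rule that both elevated measurements must fall at least 6 weeks after the start of RAS treatment is not needed. It would be a stricter definition than the protocol sets.

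The cost is one or two extra interview items, somewhat longer recall for the patient, and short wording changes. The sampling scheme, visit schedule and sample size stay as they are.
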